# A study protocol of a single-center investigator-blinded randomized parallel group study to investigate the effect of an acclimatization visit on children's behavior during inhalational sedation in a United Arab Emirates pediatric dentistry postgraduate setting as measured by the levels of salivary Alpha Amylase and Cortisol

**DOI:** 10.1097/MD.0000000000016978

**Published:** 2019-08-30

**Keywords:** acclimatization visit, anxiety, behavior, dental treatment, inhalation sedation, salivary amylase, salivary cortisol

## Abstract

Supplemental Digital Content is available in the text

## Introduction

1

Inhalation sedation (IHS) is a light form of sedation. It is a mixture of nitrous oxide and oxygen breathed through a nosepiece. This helps the child to feel relaxed and accept treatment.^[1,2]^ It is well-known that dental fear and anxiety are most common barriers to seeking dental treatment. It has been reported that approximately 23 million people with dental fear would be more willing to visit a dentist if they have been offered a form of sedation.^[3]^

The use of IHS or general anesthesia (GA) is recommended to facilitate dental treatment when nonpharmacological behavior management techniques fail to alleviate children's anxiety and fear,^[2]^ especially in the United Arab Emirates (UAE), a country with high prevalence of dental caries.^[4,5]^

The administration of nitrous oxide IHS for dental procedures is highly dependent on the child's acceptance of and keeping the nitrous oxide nosepiece in place as, at the levels used for dental procedures, it only provides a mild level of sedation and anxiolysis.^[1,2]^

It is postulated that the use of an acclimatization (familiarization) visit which can be defined as one in which sedation is only provided and no, or minimal dental intervention, is carried out would increase the acceptance and hence the efficacy of the nitrous oxide IHS.^[2]^ This method can be controversial as on one hand it may increase acceptance based on desensitization and acclimatization principles underpinning many behavior management techniques. On the other hand, it exposes the child to an additional pharmaceutical intervention and increases contact time which may influence patient compliance.

The use of an acclimatization visit has been suggested in the literature. For example, Andlaw (1996) recommended the use of an acclimatization visit before dental treatment under nitrous oxide IHS.^[6]^ The United Kingdom Royal Colleges of Surgeons and the Royal College of Anaesthetists in 2015 recommended a preparatory visit before actual treatment visit for assessment purposes for suitability for sedation.^[7]^ The Scottish Dental Clinical Effectiveness Programme (SDCEP) in 2017 also recommended the use of introductory (acclimatization) visit.^[2]^

Although authors suggested/recommended the use of an acclimatization visit, to our knowledge the existing literature does not provide any information about the efficacy of the use of an acclimatization visit of nitrous oxide sedation on the acceptance of the pediatric patients for the procedure and whether this introductory visit would result in a reduction in the stress level and an improvement of the patients’ behavior during the procedure.

Measuring dental anxiety through clinical observation is of limited value as it relies on subjective assessment.^[8]^ The lack of standardized dental anxiety measuring technique highlights the immense need for an objective assessment that will overcome the human bias encountered with the routinely used subjective assessments. A considerable amount of literature has been published on saliva as a noninvasive biological biomarker of stress.^[9]^ One of the major enzymes of saliva is salivary alpha amylase (SAA). Synthesized and secreted by acinar cells of the salivary glands, mainly the parotid gland.^[10]^ Several studies have reported the correlation between dental anxiety and the increase in SAA and cortisol levels.^[11]^ The present study set out to assess the values of SAA and salivary cortisol levels as measures of anxiety in children to compare the effect of an acclimatization visit of IHS before dental treatment with those treated routinely without an acclimatization visit.

### Study aim

1.1

This single-center, single blinded, parallel group randomized controlled two arm superiority trial aims to study the effect of a 15 minutes nitrous oxide IHS acclimatization visit on the behavior and anxiety levels of children going through dental treatment as measured by the SAA and Cortisol levels and to compare this effect with the children who go through dental treatment under IHS without the acclimatization visit.

### Research hypothesis

1.2

The utilization of an acclimatization visit of nitrous oxide sedation before commencement of treatment will result in improvement in child's behavior and reduction in the anxiety levels during dental treatment as measured by the salivary Amylase and Cortisol levels.

## Methods

2

The proposed study is a single-center, single blinded (to the dentist providing dental treatment), parallel group randomized controlled two arm superiority trial, adhering to the guidelines of the SPIRIT 2013 ^[12]^

Proposed start date: September 1st, 2019Proposed end date: February 28th, 2020

### Primary outcome

2.1

Improvement in behavior and anxiety levels. The primary outcome measured by:

(1)Physiologically by measuring anxiety-related changes using salivary levels of Alpha Amylase and Cortisol.(2)Anxiety scores at baseline (initial visit) and after treatment (second visit) using a component from the indicator of sedation need (IOSN).(3)Behavior score will be recorded using, Frankl behavior rating scale (FBRS).

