### Secondary outcomes

2.2

The following significant outcomes will be classified as evidence of beneficial effect of the acclimatization IHS visit: satisfactory completion of the required dental treatment and children's and parents’ acceptance of dental treatment with or without acclimatization visit. The secondary outcomes are measured by:

(1)Guardian/child quantitative questionnaire.(2)Records from clinical notes

All the parents of children aged 5 to 15 years referred for pediatric specialist treatment in Dubai Dental Hospital in need of treatment under IHS within 6 months’ period will be invited to participate in the study. Inclusion criteria will include: healthy children with American Society of Anesthesiologists (ASA) classification of I or II aged 5 to 15 years in need of dental treatment under IHS, with no learning disabilities and suitable for nitrous oxide/oxygen IHS. UAE and non-UAE nationals’ parents and children will be eligible to participate in the study. Included children should have no previous experience of nitrous IHS. Exclusion criteria will include children with special healthcare needs and/or medically compromised, as well as those with complex medical history (ASA III, ASA IV) or diagnosed with a psychiatric disorder, children who lack communication due to language barrier. Participants will also be excluded if their parents refuse to sign the consent.

A flowchart of the study design is presented in Figure 1.

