#### Development of the research question and outcome measures informed by patients’ priorities, experience, and preferences

2.4.1

A survey on the preference for the use of a familiarization to IHS before commencement of treatment was carried out involving 15 children, aged 5–15 years. The results were inconclusive with eight out of 15 children expressing preference for starting treatment without familiarization to sedation. This formed our primary outcome measure on comparing changes in self-reported anxiety scale in children who have familiarization visit and those who do not.

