### Statistical analysis

2.8

Data analysis will be conducted, after investigating distribution normality, with the appropriate parametric or non-parametric statistical tests using the statistical software SPSS 24.0.0 (^©^SPSS Inc, Chicago, Ill). The level of significance will be set at *P* < .05. Use of Descriptive statistics and quantitative data will be analyzed using means and standard deviations if normally distributed or medians and interquartile range if skewed. Mean changes of anxiety scores and corresponding 95% confidence intervals will be determined to compare the two treatments (sedation with familiarization and sedation without familiarization). *T*-tests will be used to compare quantitative data if normally distributed or Mann–Whitney *U*-test if skewed. The Chi-square test will be used to investigate association of categorical data. Box plots, individual and mean profiles of anxiety scores at each assessment time point for each treatment will be produced.

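### Four measures share the primary outcome with no rule for success, another section names only one of them, and the 80% power is tied to none

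*Protocol article*

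**What the plan says.** Section 2.1 (Primary outcome) begins "Improvement in behavior and anxiety levels. The primary outcome measured by" and gives three numbered items. The first, "Physiologically by measuring anxiety-related changes using salivary levels of Alpha Amylase and Cortisol", contains two assays. The second is an anxiety score at the initial visit and after treatment, taken from one component of the indicator of sedation need. The third is the Frankl rating. That makes four measures, with no statement of which decides.

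Section 2.4.1 (patient involvement in the research question) says, after reporting a survey of 15 children: "This formed our primary outcome measure on comparing changes in self-reported anxiety scale in children who have familiarization visit and those who do not".

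Other parts of the article lean in other directions:

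- The title, the aim (1.1) and the hypothesis (1.2) tie the effect to salivary amylase and cortisol.
- Section 2.3 takes the sample size from earlier studies whose measures evaluated behavior. It gives no endpoint, effect size or standard deviation.
- Section 2.8 says "The level of significance will be set at" P < .05, with a t-test or Mann–Whitney test for quantitative data. No order or split among the primary measures is given.
- Section 2.2 says of the secondary outcomes: "The following significant outcomes will be classified as evidence of beneficial effect of the acclimatization IHS visit".

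**The concern.** A superiority claim needs one stated condition for success. Here the biomarkers, the self-reported anxiety score and the behavior score can each be defended as the primary measure from the article's own text. The choice could therefore be made after the results are known. Until the rule is fixed, neither the 5% error rate nor the 80% power refers to a defined event.

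This matters because the discussion intends the result to inform guidelines on whether children should have a separate acclimatization session. A conclusion resting on whichever measure happened to reach P < .05 would be weaker evidence than it appeared.

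**Working it through.** **Inputs.** Four primary measures (section 2.1). Level 0.05 (section 2.8), taken as two-sided because the article does not say. Power 80% and 30 patients before dropout (section 2.3). The article gives no correlation between measures, so a range from 0 to 0.9 is assumed.

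**The plan's own figure.** The 30 cannot be reproduced, because no effect size or standard deviation is given. Reading it as 30 per group fits the dropout step: 30/(1 − 0.25) = 40, the number recruited per group. (At 20% and 30% dropout the step gives 38 and 43.) Solving backwards for the standardized difference:

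d = (z₀.₉₇₅ + z₀.₈₀) × √(2/n) = (1.960 + 0.842) × √(2/30) = 0.72, or 0.74 with the t distribution.

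If 30 were the total, 15 per group, d would be 1.02 (1.06 with t). These values are inferred and are not stated in the article.

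**Rule A: any one of four suffices.** With independent measures the false-positive chance is 1 − 0.95⁴ = 18.5%.

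**Rule B: all four must succeed.** Under the null for any one measure, the chance that all four reject cannot exceed that measure's own 5%, so error is not inflated. If each has 80% power and the measures are independent, joint power is 0.8⁴ = 41%.

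With correlation, simulating 1,000,000 sets of equally correlated normal test statistics gives:

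| Correlation (assumed) | Rule A: false-positive chance | Rule A: chance that at least one succeeds | Rule B: joint power |
|---|---|---|---|
| 0 | 18.5% | 99.8% | 41% |
| 0.3 | 17.4% | 98.5% | 50% |
| 0.5 | 15.6% | 96.7% | 56% |
| 0.7 | 13.0% | 93.8% | 62% |
| 0.9 | 9.4% | 88.5% | 70% |

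The two right-hand columns assume 80% power on every measure.

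**Power of one preselected measure at 0.05/4 = 0.0125.** With 30 analysed per group and d = 0.72: Φ(2.802 − 2.498) = Φ(0.304) = 62%. With the t distribution and d = 0.74 it is 61%. Restoring 80% at 0.0125 needs 2 × (2.498 + 0.842)²/0.7234² = 42.6, so 43 analysed per group. Allowing 25% dropout, 43/0.75 = 57.3, so 58 recruited per group.

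**The case against.** The strongest reply is that the measure in section 2.4.1 is not a rival endpoint. Self-reported anxiety is item (2) of section 2.1, mentioned again in a patient-involvement narrative. Section 2.8 also singles out mean changes in anxiety scores, with 95% confidence intervals, for the treatment comparison. Further, a multiplicity method is commonly left to the statistical analysis plan, which is not shown. Both points stand as far as they go: section 2.4.1 adds no fifth measure, and the absence of an adjustment method is not in itself a fault. But four primary measures and one primary measure remain incompatible statements within the same document. Which measure is primary is a protocol matter.

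Three stronger readings are tempting and should not be adopted.

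- A reader might infer that the 5% error rate and the 80% power both fail. They fail under opposite rules. Under Rule A error inflates while the chance of a positive result rises above 80%; under Rule B joint power falls while error does not inflate.
- A reader might infer from section 2.2 that any single significant secondary outcome proves benefit, and add those tests to the error count. The sentence says neither any nor each, and significant may there mean important. No inflation figure is attributed to it here.
- A reader might take the hypothesis to require success on all four. It names behavior and anxiety as measured by amylase and cortisol and does not mention the questionnaire score, so Rule B is only one possible rule.

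**Conclusion.** The point holds as an internal contradiction with no decision rule. Following the article as written permits a success claim with a false-positive chance of about 9% to 19% if any one measure is enough. It gives a joint power of about 41% to 70% if all four are needed. The ranges rest on equally correlated, approximately normal test statistics with assumed correlation between 0 and 0.9, and the joint power also on 80% for each measure.

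On power, the supportable statement is limited. The 80% belongs to no named endpoint or effect size, so it can be neither checked nor assigned to any of the four measures. The documents do not show that power is below 80% for a particular measure.

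**What to change.** Make these changes before enrolment.

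1. Reconcile sections 2.1 and 2.4.1. Either name one primary measure, tested at two-sided 5%, and make the others secondary, or keep all four and test them by Holm at an overall 5%. Self-reported anxiety is the measure section 2.4.1 already names. The title and hypothesis centre on the biomarkers, so the choice is the sponsor's.
2. In section 2.3, name the endpoint and effect size to which the 80% refers, and restate the power for the chosen primary. The existing figure should not simply be moved to another measure: 30 analysed per group gives 80% only if the standardized difference on that measure is about 0.72 to 0.74.
3. In section 2.2, describe significant secondary outcomes as supportive.

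The cost is wording and a recalculated power statement. With a single primary, whether any power is lost depends on the effect expected on that measure. Under Holm, a preselected measure has at least about 61% power at the back-solved effect, which is its power if tested alone at 0.0125, and more if the other measures also respond. That figure is not the power of Holm's first step, which tests the smallest P value and would succeed about 74% to 98% of the time if all four measures carried the effect.

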### Secondary outcomes

2.2

The following significant outcomes will be classified as evidence of beneficial effect of the acclimatization IHS visit: satisfactory completion of the required dental treatment and children's and parents’ acceptance of dental treatment with or without acclimatization visit. The secondary outcomes are measured by:

(1)Guardian/child quantitative questionnaire.(2)Records from clinical notes

All the parents of children aged 5 to 15 years referred for pediatric specialist treatment in Dubai Dental Hospital in need of treatment under IHS within 6 months’ period will be invited to participate in the study. Inclusion criteria will include: healthy children with American Society of Anesthesiologists (ASA) classification of I or II aged 5 to 15 years in need of dental treatment under IHS, with no learning disabilities and suitable for nitrous oxide/oxygen IHS. UAE and non-UAE nationals’ parents and children will be eligible to participate in the study. Included children should have no previous experience of nitrous IHS. Exclusion criteria will include children with special healthcare needs and/or medically compromised, as well as those with complex medical history (ASA III, ASA IV) or diagnosed with a psychiatric disorder, children who lack communication due to language barrier. Participants will also be excluded if their parents refuse to sign the consent.

A flowchart of the study design is presented in Figure 1.

**Figure 1 F1:**
[figure not shown]
Flowchart of the study design.

After baseline examination by the clinical team, eligibility verification, the primary investigator will obtain the participant's assent and parents’/guardian's consent submission (Appendix I, http://links.lww.com/MD/D198), participants will be randomized to either of the two study groups (30 patients per group). The study group will include families (children and parents) who would attend a visit for prevention where IHS will be introduced and tried while the control group will be the families who would attend for a prevention visit and discussion of IHS procedure only.

Block randomization with a 1:1 allocation will be performed. Concealment of allocation will be achieved by using identical, sealed, sequentially numbered, opaque envelopes that will contain group assignment. The envelopes will be opened sequentially by a dental assistant, only after the envelope has been irreversibly assigned to each participant and will remain unknown to the clinical team.

At the initial acclimatization visit, the sedation need score will be recorded using the pediatric indicator of sedation need (p-IOSN). Acclimatization visit will be carried out by a single pediatric dentist who will not be involved in the treatment of the patients. To be consistent, an information script will be prepared and rehearsed so that the same instructions about the IHS will be delivered to all participants. During the acclimatization visit, the pediatric dentist will record the p-IOSN score based on the answers of the participants to the components of the index. At the beginning of the visit, an unstimulated salivary sample of 1.5 to 2 ml will be collected to measure the levels of Alpha Amylase and Cortisol. For the intervention group only, a 15 minutes nitrous oxide IHS will be administered without any dental procedures performed.

During the second visit, two unstimulated 1.5 to 2 ml samples of saliva will be collected 15 minutes before the start of the procedure and 15 minutes after the conclusion of the procedure. The dental treatment for both study and control participants will include administering local analgesia and restoring decayed teeth with or without pulp therapy and/or dental extractions. The intervention will be carried out by a single pediatric dentist.

The 3 components of p-IOSN (Fig. 2, Tables 1 and 2) include:

(1)the modified child dental anxiety scale (MCDASf) (Fig. 2) using the SDCEP recommended shortened MCDASf questionnaire without the last two questions (on dental sedation and general anesthesia) for all anxious children.^[13]^ The MCDASf has been used widely in many dental behavioral studies.^[14–16]^(2)the treatment complexity rank score (Table 1) records the medical status which is based on the patient's (ASA) classification (Table 2).

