### Sample size calculation

2.3

The size of the sample necessary to detect a statistically significant difference was determined with a power calculation based on the results from studies carried out using the same outcome measures to evaluate behavior.^[19]^ To achieve an 80% power to detect a difference between the two groups a sample size of 30 patients was required. To compensate for dropout rate of 20% to 30%, that is, we decide to recruit 40 children in each group.

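### The protocol randomises 30 children per group in one place and recruits 40 per group in another, and neither number holds 80% power over the whole stated 20% to 30% dropout range

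*Protocol article*

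**What the plan says.** Three statements in the protocol article bear on the number of children.

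- Design text after Figure 1 (under section 2.2): once eligibility is verified and assent and consent are obtained, "participants will be randomized to either of the two study groups (30 patients per group"). The same text says "Block randomization with a 1:1 allocation will be performed", with allocation concealed in sequentially numbered sealed envelopes.
- Section 2.3, Sample size calculation: "To achieve an 80% power to detect a difference between the two groups a sample size of 30 patients was required". It does not say whether this is per group or in total.
- Section 2.3, next sentence: "To compensate for dropout rate of 20% to 30%, that is, we decide to recruit 40 children in each group".

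The calculation is described as "based on the results from studies carried out using the same outcome measures to evaluate behavior"; the article gives no effect size or standard deviation. Section 2.8 adds: "The level of significance will be set at *P* < .05", without saying whether tests are one- or two-sided.

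**The concern.** The number randomised is given two ways: 60 children in the design text and 80 in section 2.3. Randomisation comes after consent, and no loss between recruitment and randomisation is described that could turn 40 per group into 30. The 40 is itself counted within each group, so it cannot be a pool from which 30 are later randomised.

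The figure determines how many envelopes are prepared, when recruitment stops and what power the trial has. A team working from the design text would stop at 60 children and have nothing in reserve for a dropout that section 2.3 expects to be substantial.

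A second, smaller question is whether 40 per group covers the dropout range given as its reason.

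**Working it through.** **Inputs.** From section 2.3: 30 required for 80% power (read as per group), dropout 20% to 30%, 40 recruited per group. From the design text: 30 randomised per group, 1:1 allocation. From section 2.8: 5% significance level and a t-test (Mann–Whitney if skewed). Two-sided testing is an assumption.

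**Step 1: can the 30 be reproduced?** No. Without an effect size and standard deviation, the step to 30 cannot be checked. It is accepted as given below.

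**Step 2: from 30 to 40.** To keep 30 evaluable, the number to randomise is 30/(1 − dropout):

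- 20%: 30/0.80 = 37.5, so 38 per group
- 25%: 30/0.75 = 40 per group
- 30%: 30/0.70 = 42.9, so 43 per group

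The protocol's 40 is therefore reproduced exactly at 25% dropout. At 30% it is 3 per group short. Multiplying by (1 + dropout) instead gives 36 to 39, and 40 would then appear to cover the whole range, but that formula does not return 30 evaluable children after the loss.

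**Step 3: children remaining.**

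- 30 randomised: 30 × 0.80 = 24; 30 × 0.70 = 21
- 40 randomised: 40 × 0.80 = 32; 40 × 0.75 = 30; 40 × 0.70 = 28

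**Step 4: power.** The standardised difference giving exactly 80% power with 30 per group is back-solved and then held fixed.

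- Two-sided 5% t-test: 0.736.
- Two-sided normal approximation: (1.960 + 0.842) × √(2/30) = 0.723, with power = Φ(0.723 × √(n/2) − 1.960). For n = 28: 0.723 × 3.742 − 1.960 ≈ 0.75, and Φ(0.75) ≈ 0.77.
- One-sided 5% normal approximation: 0.642.

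| Randomised per group | Dropout | Remaining per group | Power, t-test | Power, normal two-sided | Power, normal one-sided |
|---|---|---|---|---|---|
| 30 | 20% | 24 | 70.4% | 70.7% | 71.9% |
| 30 | 30% | 21 | 64.3% | 65.0% | 66.8% |
| 40 | 20% | 32 | 82.6% | 82.5% | 82.2% |
| 40 | 25% | 30 | 80.0% | 80.0% | 80.0% |
| 40 | 30% | 28 | 77.1% | 77.2% | 77.6% |

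The choice of method or sidedness does not change the picture. With 43 randomised per group, 43 × 0.70 = 30.1 remain at 30% dropout, and power is 80.1% (two-sided normal).

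**Step 5: the other reading of 30.** If 30 were the total (15 per group), the implied effect would be 1.06 and even 21 per group would give about 92% power. The power shortfall would vanish, but the conflict between 60 and 80 children would not. The step from 30 to 40 in each group makes sense only if 30 is per group, which is also how the design text uses it.

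**The case against.** Section 2.3 is the dedicated sample size section and shows how 30 required becomes 40 recruited. The intent can be inferred, and the design text probably just carries over the evaluable number. That is a fair reading, but the design text says 30 are randomised, not that 30 are expected to be evaluable. It is also the passage that governs allocation, so the correction is still needed.

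The two numbers do not fail alike. Forty per group reaches 80% at the midpoint of the dropout range and loses at most about 3 percentage points at the upper end. Inflating for the midpoint of a guessed range is ordinary practice, and section 2.3 does not expressly promise 80% at 30% dropout. This stands: taken alone, the shortfall at 40 would be a minor remark.

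The power values are conditional. They depend on a back-solved effect, on 30 being the exact requirement and on 30 being per group. This also stands, and the figures should be read as what follows from the protocol's own claim, not as independent estimates.

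Lastly, the article gives no envelope count, and the flowchart in Figure 1 is not available in the text reviewed. That there would be 60 envelopes is an inference from 30 per group. The conflict between the two written statements does not depend on it.

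**Conclusion.** The concern holds. The number randomised is stated as 60 children in the design text and 80 in section 2.3, and this must be settled before envelopes are prepared.

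Following the design text puts power about 10 to 16 points below the stated 80% (70% to 64%), and below it at every dropout rate in the stated range. Following section 2.3 meets 80% from 20% to 25% dropout and falls to about 77% at 30%. It is therefore correct that neither number delivers 80% across the whole range, but the failure at 30 per group is substantial and the one at 40 is small.

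The contradiction rests on the text alone. The power figures assume that 30 is per group and gives exactly 80% power, and that a two-sided 5% t-test is used.

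**What to change.** 1. In the design text after Figure 1, change the number randomised to 40 per group (80 in total), and prepare envelopes to match. Check that the flowchart carries the same number.
2. In section 2.3, state that 30 is the number of evaluable children per group.
3. In section 2.3, state that 40 per group keeps 80% power up to 25% dropout, and that at 30% dropout 28 per group remain with about 77% power. Give the effect size and standard deviation behind the 80%, so that the 77% can be traced.

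The cost is a wording change in two places and the right number of envelopes. No child is added beyond the 80 in section 2.3, and the stated power becomes slightly less favourable at the upper end of the dropout range.

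If the sponsor wants 80% power over the whole stated range, 43 per group (86 in total) achieves it, at a cost of 6 more children.

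### The baseline anxiety score is recorded after randomization, at no fixed point in an arm-specific visit, by the dentist who gives the gas, so the anxiety change score can be biased at its starting point

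*Protocol article*

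**What the plan says.** All points are from the protocol article.

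- **Order.** In the procedures text around Figure 1, baseline examination, eligibility verification and consent come first, and then "participants will be randomized to either of the two study groups (30 patients per group"). The initial visit follows.
- **The visit differs by arm.** Study-arm families "would attend a visit for prevention where IHS will be introduced and tried while the control group will be the families" who attend for prevention and a discussion of inhalation sedation only. Later in the same text: "For the intervention group only, a 15 minutes nitrous oxide IHS will be administered without any dental procedures performed".
- **Who runs it.** "Acclimatization visit will be carried out by a single pediatric dentist who will not be involved in the treatment of the patients".
- **Baseline anxiety.** "During the acclimatization visit, the pediatric dentist will record the p-IOSN score based on the answers of the participants". No position within the visit is given.
- **Baseline saliva.** "At the beginning of the visit, an unstimulated salivary sample of 1.5 to 2 ml will be collected".
- **Concealment.** A dental assistant opens the envelopes, and allocation "will remain unknown to the clinical team". When an envelope is opened relative to the baseline measures is not stated. The Methods opening limits blinding to the dentist who provides the dental treatment.
- **Use of the baseline.** Section 2.1 lists, as one of three primary measures, "Anxiety scores at baseline (initial visit) and after treatment (second visit"). Section 2.8 compares mean changes of anxiety scores between the arms, with t-tests or Mann–Whitney tests for quantitative data, and names no baseline-adjusted model.

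**The concern.** A change score is protected by randomization only if its starting value cannot depend on the arm. Here the starting value is obtained after randomization, at the visit where the arms diverge, and the text allows two routes by which the arm could reach it.

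1. **Knowledge of the arm.** A child who expects to try the gas that day may answer the faces scale differently from one who expects only a talk. A dentist who knows the arm may prompt differently. If this raises the intervention arm's baseline, the excess later appears as improvement.
2. **The gas itself.** If the score is recorded after the 15 minutes of nitrous oxide, the baseline already contains the intervention's effect, and a real benefit could be hidden.

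The two routes can work in opposite directions, so the sign of any bias could not be judged from the results. A baseline recorded too late cannot be taken again.

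The concealment sentence also conflicts with the visit description. The dentist who gives gas to one arm and not the other knows each child's arm by that point.

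**Working it through.** **Step 1: the text side by side.**

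| Element | Timing in the protocol | Arm known or gas given by then? |
|---|---|---|
| Randomization | Before the initial visit | – |
| Saliva, baseline | Beginning of the visit | Gas: not by the order described. Arm: not stated |
| p-IOSN / MCDASf, baseline | During the visit | Gas: not excluded. Arm: not excluded |
| Nitrous oxide | During the visit, intervention arm only | Visit dentist necessarily knows |
| Frankl score | No baseline stated | Not reached by this route |

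No anxiety or saliva measure before randomization is described. One baseline measure is fixed in time and the other is left open. Sentence order does not settle it, because the sentence on recording the p-IOSN stands before the one on saliva at the beginning of the visit. The narrative is therefore not strictly chronological.

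**Step 2: group size for the illustration.** The procedures text gives 30 per group. Section 2.3 recruits 40 per group to allow for 20% to 30% dropout. 30/(1 − 0.25) = 40, so 30 is consistent with the number analysed after losses. The protocol gives no effect size, SD or correlation.

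**Step 3: effect of a shifted baseline.** Assumptions: no true effect, equal SD at both visits, two-sided 5% test, normal approximation, pre–post correlation ρ, and a differential baseline shift of s SD with no shift at follow-up.

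- Bias of the change score = s.
- SE of the change-score difference = √(2 − 2ρ) × √(2/n).
- Rejection rate = Φ(s/SE − 1.96) + Φ(−s/SE − 1.96).

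With n = 30 and ρ = 0.5, SE = 1 × √(2/30) = 0.258.

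- s = 0.2: s/SE = 0.775, rejection rate 12.1%.
- s = 0.3: s/SE = 1.162, rejection rate 21.3%.

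Non-central t with 58 degrees of freedom gives 11.9% and 20.8%.

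**Step 4: baseline adjustment (ANCOVA).** Bias = ρs and SE = √(1 − ρ²) × √(2/n). With n = 30 and ρ = 0.5, SE = 0.866 × 0.258 = 0.224.

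- s = 0.2: bias 0.10, rejection rate 7.3%.
- s = 0.3: bias 0.15, rejection rate 10.3%.

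**Step 5: range over the assumed correlation, 30 per group.**

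| Shift | Method | ρ = 0.3 | ρ = 0.5 | ρ = 0.7 |
|---|---|---|---|---|
| 0.2 SD | Change score | 10.0% | 12.1% | 17.0% |
| 0.2 SD | ANCOVA | 5.7% | 7.3% | 11.8% |
| 0.3 SD | Change score | 16.6% | 21.3% | 32.3% |
| 0.3 SD | ANCOVA | 6.5% | 10.3% | 20.7% |

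With 40 per group and ρ = 0.5, the change-score figures are 14.5% and 26.9%. A larger sample makes a fixed bias easier to mistake for an effect.

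**The case against.** The strongest reply is that bias is assumed rather than shown. Randomizing before measuring is not itself a bias: the arm must be known, or the gas given, before the score is taken. The protocol does not say when the envelope is opened relative to the score. Figure 1 is not available here and may show the order, and an article may leave steps within a visit to the full protocol. The dentist records the child's own answers on a faces scale, the items on sedation and general anesthesia are left out, and the same dentist and rehearsed script serve all participants. Clinical team could also be read as the treating team, given the blinding statement in Methods.

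Much of this stands and limits the point:

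- A reader might infer that all baseline measures are compromised. Saliva is taken at the beginning of the visit and assayed under a code number, so the recorder cannot move it. Only anticipation could, and only if the family already knows the arm.
- A reader might infer that the whole primary outcome is affected. The Frankl score has no stated baseline, and which saliva samples form the change is not stated. Only the anxiety measure is explicitly tied to the initial visit.
- A reader might infer that the dentist rates the child's anxiety. The exposure is narrower: prompting and timing.
- A reader might infer that an entry criterion is scored only after randomization. No p-IOSN score or threshold is an entry criterion. Eligibility, including need for inhalation sedation, is verified before randomization, and section 2.4.3 says recruits are already indicated for such treatment.

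What does not stand is that nothing needs changing. The article fixes the time of one baseline measure and leaves the other open, so a score taken after the gas would comply with it. No flowchart can make the concealment sentence true of the dentist who gives the gas, unless the team is defined to exclude that dentist.

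**Conclusion.** The concern holds for the anxiety change score and for the concealment sentence. As written, the protocol permits a baseline anxiety score taken after the arm is known or after the gas. It does not establish that this will happen.

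The 12% and 21% figures are illustrations, not estimates for this trial. They rest on assumed shifts of 0.2 and 0.3 SD, an assumed correlation of 0.5, 30 analysed per group and no true effect. They size the false-positive side; a score taken after the gas would more likely conceal a benefit. Adjustment for baseline softens the problem without removing it, and no adjusted model is named in section 2.8.

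That the arm may matter to children is plausible but not shown. In the survey in section 2.4, eight of 15 preferred to start without familiarization, while 10 of 15 were not overly concerned about which arm they would get.

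The change should be made before enrolment, because the weakness touches a primary measure, prevention costs little, and a late baseline cannot be re-measured.

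**What to change.** - **Order at visit 1.** Collect the saliva sample and complete the MCDASf and p-IOSN first, with only the common script as information. Open the envelope after that, so that dentist and family learn the arm once baseline is complete and before any gas.
- **Concealment sentence.** State that allocation is unknown to everyone until baseline is complete and to the treating dentist throughout, and that the acclimatization-visit dentist is unblinded after baseline.

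The cost is a reordering of steps within an existing visit and a change of wording, with no added visit or staff. One small downside is that the gas equipment must be available at every first visit, because the arm is not known beforehand.
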